### Statistical analyses

#### Analytical principles

Analyses will be conducted according to the intention-to-treat principle [2] if not otherwise stated.

All primary tests of significance will be two-sided with alpha = 5%. Analyses will be conducted blinded with the two intervention groups coded as, e.g. 0 and 1. Two conclusions will be drawn, one assuming 0 is the intervention group and 1 is the control, and one assuming the opposite. After two abstracts with two conclusions have been written and both accepted by the Steering Group, the code will be broken.

The primary analyses of primary, secondary, and exploratory outcomes will be those of the intention-to-treat population adjusted for the protocol-specified stratification variable and the minimisation variables, and if necessary using data sets generated using multiple imputation.

#### Missing values of the primary outcome

By definition, none of the adjusting variables will have missing values (otherwise the stratification and minimisation could not have been conducted). So only the outcome value may be missing. Furthermore, we assume there are no useable auxiliary variable, i.e. no other variable that has a moderate to high correlation with the outcome (|r| > 0.40) and yet is not intended to be a predictor in the regression model. In this situation, the problem is easily solved. If we are willing to assume that the data are missing at random, the maximum likelihood analysis reduces to a complete case analysis [3, 4]. Consequently, we simply delete participants that are missing on the outcome and estimate the regression with the remaining participants. However, if useable auxiliary variables have been identified, a multiple monotone imputation will be conducted, which will include the primary outcome and the covariates of the analytical model plus the auxiliary variables. As a sensitivity analysis to assess the potential impact of outcome values missing not at random (MNAR), we will conduct a worst/best case scenario imputation, i.e. a single value imputation of the missing values. The imputations use a minimum value or a maximum value (0 respectively 5 of the modified Rankin scale in that we assume that a patient who died will not have the mRS value missing). Missing values are imputed by the minimum value in one intervention group, and in the other intervention group by the maximum value and vice versa. Once the randomisation code is broken the results of the two comparisons may be interpreted.

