**Fig. 1 Fig1:**
[figure not shown]
Overview of patient schedule and data collection in the EuroHYP-1 trial (*grey tone* only for the experimental group). 1 Re-warming: hypothermia group only. 2 Previous medication including alteplase. 3 Includes sodium, potassium, magnesium, creatinine, urea, gamma-glutamyl transpeptidase, ASAT, ALAT, alkaline phosphatase, blood glucose; haemoglobin, haematocrit, erythrocytes, leukocytes, platelets, INR. Further samples may be taken throughout the study at the discretion of the investigator. 4 Body temperature will be assessed according to local clinical practice with tympanic, bladder, or rectal temperature measurement, except in patients randomised to therapeutic hypothermia from start of treatment phase (TP, beginning of hour 1) until end of re-warming period, when bladder or rectal thermal probes will be used. During TP, body temperature will be assessed every 15 min during the first 3 hours (except at time points t = 0 min and t = 15 min) and every 60 min thereafter in patients randomised to therapeutic hypothermia, every 60 min (except at time point t = 0 min) in patients randomised to best medical treatment alone, subsequently in all patients at 8-hour intervals until A6 (day 8 or day of discharge from hospital, whichever occurs first). 5 The mRS assessment at outcome assessment (A7) will be recorded using a digital video camera. The clip will then be transferred to the EuroHYP-1 outcome adjudication web portal. 6 Anti-shivering medication: induction: buspirone 10 mg p.o./pethidine 50 mg i.v. (2 min); repeat doses of 10 mg buspirone p.o. may be administered as long as a maximum dose of 30 mg/24 h is respected; a bolus of pethidine 25 mg i.v. may be given as long as an interval of at least 30 min is respected and a maximum dose of 500 mg/24 h is not exceeded. 24 h-doses include induction bolus. For the prevention and treatment of opioid-induced nausea and vomiting, a 5HT3RA may be administered as support medication. 7 Induction of cooling: 20 ml/kg estimated bodyweight 4 °C isotone saline or Ringer´s lactate over a period of 30–60 min; EMCOOLS Brain.Pad, if available. 8 IMDs permitted for cooling: EMCOOLS Brain.Pad (for induction of cooling only); Medivance/Bard Arctic Sun temperature management system with heat exchange control unit Arctic Sun 2000 or Arctic Sun 5000 and ArcticGel Pads; MTRE CritiCool temperature management system with heat exchange control unit CritiCool, accessoires and CureWrap; Zoll IVTM system with heat exchange control unit CoolGard 3000 or Thermogard XP, CoolGard start-up kit and intravascular temperature management catheters ICYy 3893 AE or ICY 3893 CO. 9 If endovascular cooling is performed, the catheter insertion site must be visually inspected for detection of bleeding/haematoma in 3-hour intervals during TP and once 3 hours after removal of the intravascular catheter. 10 Monitoring for pneumonia includes monitoring of oxygen saturation and body temperature, physical examination (auscultation, percussion) and, if clinically indicated, chest X-ray. Monitoring for signs of pneumonia must be performed from screening assessment (A1, within 90 minutes before the start of the treatment phase TP) until A6 (day 8 or day of discharge from hospital, whichever occurs first). 11 Patient location during stay in hospital must be assessed at 12:00 hours on each day in hospital. 12 WHODAS 2.0 questionnaire and EQ-5D questionnaire must be filled in by the patient or his/her relative/carer at outcome assessment (A7). 13 Health Recovery Guide and Diary: Section 6: filled in by the patient every day from discharge to V7; Section 7: filled in by the carer/relative prior to V7. 14 For participation in the biomarker sub-study a special informed consent form must be filled in by the patient or his/her legal representative. Assessment at End of Hour 24 ± 2 hours. 15 Only selected study sites. 16 Informed consent will be obtained in accordance with national regulatory requirements. 17 NIHSS assessment at End of Hour 24 ± 2 hours. 18 Starting at t = 30 min. 19 Every 60 minutes only. 20 Prior to intended repeat administration of pethidine. *CT* computed tomography, *ECG* electrocardiogram, *EQ-5D-5 L* EuroQoL quality-of-life scale, GCS Glasgow coma scale, *MRI* magnetic resonance imaging, *NIHSS* National Institutes of Health Stroke Score, *SAE* serious adverse event, *WHODAS* World Health Organization Disability Assessment Schedule

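### Deleting participants with a missing mRS as missing at random conflicts with the plan's assumption that the dead are never missing; known survival is discarded and the primary odds ratio can be biased

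*SAP article*

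**What the plan says.** All of the following is in the section on missing values of the primary outcome unless another place is named.

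- The adjusting variables are complete by design, so only the outcome can be missing. The plan then starts from the premise that "we assume there are no useable auxiliary variable", meaning no variable outside the model with |r| above 0.40 with the outcome.
- The justification for the default is "If we are willing to assume that the data are missing at random, the maximum likelihood analysis reduces to a complete case analysis". The resulting rule is "Consequently, we simply delete participants that are missing on the outcome and estimate the regression with the remaining participants".
- There is a second branch: "However, if useable auxiliary variables have been identified, a multiple monotone imputation will be conducted". Its imputation model contains the primary outcome, the model covariates and the auxiliary variables. Vital status is not listed, and no range is set for the imputed values. Analytical principles also allows multiple imputation where necessary.
- The sensitivity analysis for data missing not at random uses mRS 0 and 5: "Missing values are imputed by the minimum value in one intervention group, and in the other intervention group by the maximum value and vice versa". The stated reason for 5 rather than 6 is that "we assume that a patient who died will not have the mRS value missing".
- The schedule in Fig. 1 includes "NIHSS assessment at End of Hour 24 ± 2 hours". The adjusting variables are country and the seven minimisation factors, so this later NIHSS is not a predictor in the model.

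**The concern.** The two assumptions in this section do not fit together. If the dead always have an mRS (6), the probability of a missing mRS is 0 at level 6 and positive only within 0–5. Given the covariates, missingness then depends on the outcome itself. That is not missing at random for the model the plan fits.

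The likelihood statement fails for the same reason. Reduction to complete case is correct when the only incomplete variable is the outcome, it is missing at random, and nothing further is known about it. Here something is known: on the plan's own premise, each participant without an mRS has a value in 0–5. That is partial information on the primary outcome, and deletion discards it.

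What is at stake is the primary estimate. Deleting only survivors raises the share of mRS 6 among the observed values in both arms. If the arms lose survivors at different rates, the common odds ratio moves off its true value.

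**Working it through.** **Inputs from the SAP article.** Control mortality 17%, control mRS > 2 63% and common odds ratio (OR) 0.74 (Power of the original secondary outcomes); N = 800; two-sided α = 5%; 3% loss to follow-up, from the original plan for 1500 patients (The sample size).

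**Assumed.** 1:1 allocation; control mRS 0–6 of 10, 13, 14, 14, 20, 12 and 17% (only the 17% and the 63% above 2 come from the article); loss by arm. The refit is not adjusted for covariates.

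**Step 1: the plan's own figures.** Control odds of death are 0.17/0.83 = 0.2048. Multiplying by 0.74 gives 0.1516, hence a risk of 0.1316 and x = 0.0384, as stated. Power with 400 per arm is 0.329 (stated 0.33). For mRS > 2, 63% v 55.75% gives 0.551 (stated 0.55). Under the assumed distribution, OR 0.74 with 1455 evaluable of 1500 gives power 0.906, consistent with the stated 10% type 2 error.

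**Step 2: the mechanism at two cut-points.** Take a true OR of 1 and random survivor loss of 4% of the control arm and 2% of the cooled arm (mean 3%).

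- Cut at 6, among observed mRS values: control 0.17/(0.83 − 0.04) = 0.2152; cooled 0.17/(0.83 − 0.02) = 0.2099; ratio 0.975.
- Cut above 2: control mRS 0–2 is 0.37 × (1 − 0.04/0.83) = 0.3522, odds (0.96 − 0.3522)/0.3522 = 1.726. Cooled is 0.37 × (1 − 0.02/0.83) = 0.3611, odds (0.98 − 0.3611)/0.3611 = 1.714. The ratio is 0.993.

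The fitted common OR averages over the cut-points.

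**Step 3: proportional-odds refit on complete cases.** The model is fitted by maximum likelihood to the expected counts. Type I error uses z = ln(OR) × √V with V = (n/12)(1 − Σp̄³). At n = 776 the standard error is about 0.126. Loss is a share of each arm.

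| Loss, control / cooled | Survivors lost | True OR 1 becomes | Two-sided type I error | True OR 0.74 becomes |
|---|---|---|---|---|
| 3% / 3% | at random | 1.000 | 0.050 | 0.739 |
| 4% / 2% | at random | 0.989 | 0.051 | 0.732 |
| 6% / 0% | at random | 0.967 | 0.058 | 0.717 |
| 0% / 6% | at random | 1.034 | 0.058 | 0.761 |
| 4% / 2% | mRS 0–2 only | 0.960 | 0.062 | 0.705 |
| 6% / 0% | mRS 0–2 only | 0.884 | 0.17 | 0.652 |
| 4% / 2% | mRS 3–5 only | 1.013 | 0.051 | 0.749 |
| 6% / 0% | mRS 3–5 only | 1.040 | 0.061 | 0.774 |

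**Step 4: the planned 0/5 analysis.** At 3%/3% it spans 0.88 to 1.14 under a true OR of 1, and 0.65 to 0.86 under 0.74.

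**Step 5: using survival.** Each participant with a missing mRS contributes ln P(mRS ≤ 5) to the log-likelihood instead of being deleted. With random survivor loss at 4%/2%, 6%/0% and 0%/6%, the refit returns 1.000 under a true OR of 1 and 0.740 under 0.74. Loss that depends on mRS level is not repaired. At 6%/0% under a true OR of 1, loss confined to mRS 0–2 gives 0.914 (complete case 0.884), and loss confined to mRS 3–5 gives 1.075 (complete case 1.040).

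**The case against.** The strongest reply has four parts.

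- **Deletion is one branch.** If an auxiliary variable is found, the plan imputes, and the table of amendments lists the search for auxiliaries as a deliberate change. This is true. But the branch names no candidates, does not mention vital status, and leaves a participant taken to be alive open to an imputed 6. The amendments table gives efficiency, not bias, as its reason.
- **The plan has an analysis for data missing not at random.** The 0/5 imputation respects survivor-only missingness, and its span at 3%/3% contains the random-loss shifts in Step 3. This stands, but it does not change the primary estimate.
- **The size is modest.** At 4%/2% random loss the shift in the log OR is ln 0.989 = −0.011, about 0.09 standard errors. The article gives no basis for assuming loss confined to mRS 0–2. This stands, and it limits the claim.
- **The auxiliaries may help little.** EQ-5D and WHODAS are completed at the same assessment as the mRS and may be missing with it. The power text for infarct size uses 250 participants. This stands too, and makes the 24-hour NIHSS the main candidate. Its correlation with the mRS is not given.

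A reader might go further in three ways that the article does not support. One is that the comparison is biased whenever loss differs. Losses of good and poor survivors pull in opposite directions and can cancel. Another is that the separate death outcome and the worst-score scales are distorted in the same way. A participant known to be alive is not missing on death, and the deletion rule is written for the primary outcome only. The third is that knowledge of allocation drives unequal loss. The article states masked outcome assessment and says nothing on loss by arm.

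**Conclusion.** The point holds at a limited size. The justification for complete-case analysis contradicts the plan's own assumption about the dead, and the maximum likelihood sentence is wrong under that assumption. At about 3% average loss with random loss among survivors, the common OR shifts by about 1% (4%/2%) to 3% (6%/0%), in either direction. The type I error is then 0.051 to 0.058. If the same losses depend on mRS level, the shift can reach 0.884 with a type I error of about 0.17, as an extreme case. Equal loss gives exactly 1.00 under the null and 0.739 instead of 0.74 under the alternative when survivors are lost at random.

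These sizes rest on assumed loss by arm, an assumed split within mRS 0–5 and an unadjusted model. The contradiction itself rests on none of them. It should be corrected, but the material does not show that the primary result would be seriously wrong.

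**What to change.** Before unblinding, amend the section on missing values of the primary outcome:

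1. Replace the missing-at-random and maximum likelihood sentences. State that under the plan's assumption only survivors can lack an mRS, and that missingness at random is assumed given the covariates and vital status.
2. Make the primary handling a multiple imputation, or a likelihood with a term for mRS ≤ 5, that uses known vital status so that known survivors take only values 0–5.
3. Remove the premise that no auxiliary variable exists. Name already collected candidates in advance, the NIHSS at 24 hours first.
4. Keep complete case and the two-way 0/5 imputation as sensitivity analyses.
5. Report missing mRS by arm, with vital status.

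The cost is revised wording and some programming, with no new data and a slightly more complex primary analysis. Loss that still depends on mRS among survivors is not repaired. As Step 5 shows, it can move the estimate further off when poor survivors are the ones lost, so the 0/5 analysis remains necessary.

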#### The primary outcome

The primary outcome is degree of disability post stroke as measured by the seven-level modified Rankin Scale measured in the period 91 ± 14 days after the patient’s randomisation.

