#### Power of the original secondary outcomes

As the sample size is based on the primary outcome, we have calculated the power of each of the originally planned secondary outcomes given the sample size of 800 patients.

Death day 91 ± 14 days after randomisation: the implied clinically relevant minimal change in mortality that needs to be detected may be calculated based on (1) the mortality of 17% found in the meta-analysis quoted in the protocol [1]; (2) the assumption that wherever the mRS is dichotomised, the odds ratio for treatment versus control will be the same, the ‘common odds ratio’; and (3) the requirement that this common odds ratio should not be larger than 0.74 (see the sample size calculation). Let the unknown change in mortality in the experimental group be x. If we assume the OR for the dichotomy mRS > 5 compared to mRS ≤ 5 will be 0.74 and the mortality of the control group is 17% as quoted in the meta-analysis, we may find x by solving the equation OR = ((0.17–x)/(0.83 + x))/(0.17/0.83) = 0.74 to obtain x = 0.0384 giving a mortality of 0.1700 – 0.0384 = 0.1316 in the cooled patients versus 0.1700 in the controls. Using a sample size of 800 participants, the power is found to be 0.33.

Death or dependency (mRS > 2) 91 ± 14 days after randomisation: using the same reasoning, the power of this outcome can be calculated by solving the equation (0.63–x)/(0.37 + x))/0.63/0.37 = (0.63 – x)0.63/(0.37 + x)0.37 = 0.74 as 63% of the patients in the meta-analysis had mRS > 2 implying x = 0.0725. The power may then be calculated to be 0.55.

NIHSS score 91 ± 14 days after randomisation: assuming a minimal relevant difference of 2 points, a standard deviation (SD) of 5 points [5], an α of 0.05, and a sample size of 800 participants, the power may then be calculated to 1.00.

EQ-5D-5 L score 91 ± 14 days after randomisation: assuming a minimal relevant difference of 0.05 points, a SD of 0.40 points [6–9], an α of 0.05, and a sample size of 800 participants, the power may then be calculated to 0.42.

WHODAS 2.0 score 91 ± 14 days after randomisation: we originally planned to analyse the World Health Organization Disability Assessment Schedule II (WHODAS 2.0) score at outcome assessment in the period day 91 ± 14 days after randomisation. However, due to difficulties in assessing the clinical meaning, we are not able to calculate the power, and we will thus analyse this as an exploratory outcome.

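### The worst-case mRS imputation stops at 5, which bounds the result only if vital status at day 91 ± 14 is known for every participant with a missing score

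*SAP article*

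**What the plan says.** The primary outcome is "degree of disability post stroke as measured by the seven-level modified Rankin Scale". Table 3 of the SAP article has columns for mRS 0 to 6, and the section on power of the secondary outcomes equates death with the top level: "If we assume the OR for the dichotomy mRS > 5 compared to mRS ≤ 5 will be 0.74".

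Under Missing values of the primary outcome, the main approach assumes data missing at random (complete cases, or multiple imputation if useful auxiliary variables are found). One sensitivity analysis is added "to assess the potential impact of outcome values missing not at random (MNAR"). Its extremes are set as follows: "The imputations use a minimum value or a maximum value (0 respectively 5 of the modified Rankin scale in that we assume". The reason follows in the same sentence: "we assume that a patient who died will not have the mRS value missing". The direction is then fixed: "Missing values are imputed by the minimum value in one intervention group, and in the other intervention group by the maximum value and vice versa".

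No scenario imputes 6. The article does not say how vital status is established for a participant who cannot be reached.

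**The concern.** A participant may lack an mRS score for two different reasons. One is documented alive but was not scored, and 5 is then the worst value possible. The other cannot be traced, so it is unknown whether that person is alive. For the second, 5 is the worst value only if every death reaches the trial team.

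The rule treats both alike. Undetected death is itself a way for data to be missing not at random, and the only analysis of the primary outcome that addresses such missingness rules it out by assumption. Death is not remote here: the plan takes 17% control mortality. The Discussion section also takes care that deaths are not lost from the comparison of the continuous scores, by giving known deaths the worst score.

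At stake is whether the reported range can be read as the extreme range. If some missing participants have unknown vital status, it is narrower than the label worst/best case suggests.

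**Working it through.** **Inputs from the SAP article.** Control mortality 17%, control mRS > 2 63%, common OR 0.74 and 800 participants (section on power of the secondary outcomes); two-sided 5% (Analytical principles); 3% loss to follow-up, stated for the original 1500-patient design (The sample size). No loss rate is restated for 800.

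**Assumptions.** 400 per arm; equal loss in both arms; no covariate adjustment; OR 0.74 holds among observed participants. The article does not give the full control mRS distribution, so three were tried, each with 63% above 2 and 17% dead (percent at levels 0 to 6):
- A: 8, 15, 14, 16, 18, 12, 17
- B: 5, 12, 20, 20, 18, 8, 17
- C: 12, 15, 10, 12, 16, 18, 17

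**Step 1: reproduce the plan's figures.**
- Death: control odds 0.17/0.83 = 0.2048; × 0.74 = 0.1516; risk 0.1516/1.1516 = 0.1316; x = 0.0384. With pooled risk 0.1508, SE = √(2 × 0.1508 × 0.8492/400) = 0.0253; 0.0384/0.0253 = 1.52; power = Φ(1.52 − 1.96) = 0.33, as stated.
- mRS > 2: 0.63/0.37 × 0.74 = 1.26; risk 0.5575; x = 0.0725; SE 0.0347; power = Φ(2.09 − 1.96) = 0.55, as stated.

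**Step 2: cooled distribution.** The same conversion at every cut gives, for A, 10.5, 18.2, 15.5, 16.1, 16.4, 10.0 and 13.2% at levels 0 to 6.

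**Step 3: impute and refit.** With m missing per arm, observed counts are (400 − m) × proportion. In the unfavourable scenario, m controls are added at 0 and m cooled participants at 5 (the plan) or 6. The favourable scenario swaps the arms. The model is logit P(mRS ≤ k) = aₖ − b × cooled, OR = exp(b), fitted by maximum likelihood, with a likelihood-ratio p-value and SE = |b|/√(likelihood-ratio statistic).

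Unfavourable scenario, distribution A:

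| Loss (m per arm) | Worst value 5 | Worst value 6 |
|---|---|---|
| 1% (4) | OR 0.778, p = 0.043 | OR 0.785, p = 0.051 |
| 3% (12) | OR 0.86 (0.67–1.10), p = 0.22 | OR 0.88 (0.69–1.12), p = 0.31 |
| 5% (20) | OR 0.95, p = 0.66 | OR 0.99, p = 0.92 |
| 10% (40) | OR 1.20 (0.94–1.53), p = 0.14 | OR 1.30 (1.02–1.66), p = 0.033 |

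Range over A, B and C:
- 1%: p 0.040–0.046 with 5, 0.049–0.053 with 6. The threshold is crossed in two of the three.
- 3%: OR 0.85–0.87 (p 0.19–0.25) with 5, 0.88–0.89 (p 0.29–0.33) with 6.
- 5%: OR 0.93–0.96 with 5, 0.98–1.00 with 6.
- 10%: OR 1.17–1.23 (p 0.09–0.22) with 5, 1.28–1.32 (p 0.025–0.044) with 6. The threshold is crossed in all three.

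Favourable scenario at 3%: OR 0.65–0.66 with 5, 0.64 with 6.

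The 6 columns assume that every missing participant has unknown vital status. If only some do, the result lies between the two columns.

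**The case against.** The strongest reply is that 5 is no slip about the scale. It follows from an assumption stated in the same sentence, and if all deaths are ascertained, 5 is the worst score a missing participant can have. Tracing of vital status is usually a protocol matter, the protocol is not at hand, and the article's silence does not show that tracing is absent. All of this stands, and it makes the point conditional.

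A reader might go further in three ways that the document does not support.
- **That 0/5 fails to bound the result, without qualification.** It fails only if some missing participants may have died undetected, and nothing in the article says there will be any.
- **That the cap hides fragility in the benefit.** At 3% loss, 0/5 already removes significance (complete-case p about 0.017, unfavourable p about 0.22). At 10% it already reverses the direction. Significant harm with 6 needs more than three times the only stated loss rate, with all 40 missing cooled participants dead and all 40 missing controls symptom-free.
- **That the rule makes the death endpoint untestable for missing data.** The section covers the primary outcome only and defines no best/worst scenario for death as a separate endpoint. For mRS > 2, values 5 and 6 fall in the same category.

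What the reply does not remove is that a stress test for informative missingness rests on an assumption, for which the article gives no support, that excludes one informative mechanism.

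**Conclusion.** The concern holds in conditional form. The 0/5 rule is correct for participants documented alive without a score. For participants of unknown vital status it leaves out the least favourable value, so the range is a true bound only when vital status at day 91 ± 14 is known for everyone.

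The size is modest: a shift of about 0.02 to 0.03 in the unfavourable OR at 3% loss, with the same reading. The p-value crosses 0.05 only at the margins examined, about 1% loss (two of three assumed distributions) and an illustrative 10% (all three). These figures depend on the assumed mRS distributions, 1:1 allocation, equal loss, OR 0.74 among observed patients and an unadjusted model. One sensitivity analysis is affected; the primary analysis is not.

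**What to change.** In the section Missing values of the primary outcome, split the rule by vital status: impute 0 and 6 for participants whose vital status at the assessment is not confirmed, and keep 0 and 5 for those documented alive but without an mRS. If vital status turns out to be known for everyone, the new rule gives the same result as the present one.

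The cost is one sentence and a record of confirmed vital status for each participant with a missing score. The downside is a slightly wider and less favourable sensitivity range where vital status is unknown.
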